### 1.5. Outcome Measures

The primary outcome is the proportion of soft (active) carious tooth surfaces that turn hard (arrested) at the 30-month follow-up. The secondary outcomes are parental satisfaction, children’s compliance, and adverse effects of the SDF therapy.

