### 2.7. Randomisation, Treatment Allocation, and Allocation Concealment

Eligible children will be stratified based on the number of carious tooth surfaces at baseline (1 to 3 surfaces vs. more than 3 surfaces) and randomly allocated to receive either 38% SDF solution or gel. Block randomisation with a block size of 6 will be adopted to assign children to the two treatment groups. A statistician who is not involved in the clinical assessment will generate the randomisation sequence and place the group assignments in opaque sealed envelopes. During the clinical examination, once eligibility is confirmed, a research assistant will assign the randomisation envelope sequentially. This approach ensures effective allocation concealment prior to the administration of the assigned SDF intervention.

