### 2.9. Interventions

After the completion of the oral examinations by the blinded examiner at baseline and follow-ups, another dentist will apply the assigned SDF formulation to all carious lesions. According to the recommended clinical procedures, the dentist will first clean away any food debris from the carious lesions and isolate the carious tooth with gauze or cotton roll.

The dentist will dry the carious lesions with a micro-brush and apply the assigned SDF with another micro-brush on the carious lesions for 60 s. Gauze or cotton roll will be used to absorb excessive SDF [22]. The two intervention groups in this study are the following:

Group A: 38% SDF solution (Advantage Arrest 38% SDF solution, Elevate Oral Care, LLC, West Palm Beach, FL, USA) applied semi-annually, and

Group B: 38% SDF gel (Advantage Arrest 38% SDF Gel, Elevate Oral Care, LLC, West Palm Beach, FL, USA) applied semi-annually.

Children in both groups will be instructed to avoid eating or drinking for 30 min after the SDF application. The SDF therapies will be administered every 6 months for a total duration of 30 months. The parents will be informed to report any potential adverse effects, including tooth pain, allergic reactions, gingival irritation, or other issues related to the SDF treatment within 48 h. Referrals for restorative dental treatment will be provided to the children if deemed necessary. Additionally, both teachers and parents will receive information indicating that successfully arrested carious lesions may appear hardened and turn black following the SDF application.

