### 2.10. Assessment of the Children’s Compliance

A trained research assistant will assess the children’s compliance during SDF therapy (solution or gel) using Venham’s behaviour-rating scale. This validated instrument provides six scores to evaluate a child’s reactions and behaviours during dental care [23]. Table 1 shows the codes of Venham’s behaviour-rating scale.

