### 2.12. Follow-Up Evaluations

The follow-up oral examinations will be conducted semi-annually in the kindergarteners for 30 months by the same examiner using the same equipment, standardised procedure, and diagnostic criteria as used in the baseline examination. The examiner will assess the children’s dmfs index, VPI, the status of carious surfaces (classified as active or arrested through gentle probing), and visible dental plaque at carious lesions. New carious lesions will be recorded and treated with the assigned intervention. An independent, trained health practitioner will examine the children for the presence of potential adverse effects related to the SDF treatments one day after the SDF therapy. Children’s compliance with the SDF therapy will be assessed using Venham’s behaviour-rating scale. Any sign of tooth non-vitality, such as tooth hypermobility or dental abscesses, and reasons for premature tooth loss will be documented.

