### 2.15. Statistical Analysis

Data analysis will be conducted using SPSS 24.0 software (SPSS Inc., Chicago, IL, USA). Intra-examiner agreement for caries diagnosis will be evaluated using Cohen’s Kappa statistics. Non-inferiority of the SDF gel group compared with the SDF solution group (control, caries arresting rate 76.5%) will be accepted if the lower limits of the 95% two-sided CI of the difference in the caries-arresting rate is greater than the non-inferiority margin (7.65%). This test for non-inferiority will only be performed for the primary endpoint, which is the proportion of the soft (active) carious tooth lesion surfaces that turn hard (arrested) at the 30-month follow-up. An intention-to-treat approach is planned to utilise all available data from all originally recruited children.

At subject level, chi-square tests will be used to compare proportions of arrested carious surfaces between groups during the follow-ups. These statistical tests will also be applied to analyse the incidence of new carious surfaces and dropout rates between groups during the follow-ups. Independent sample t-tests will be employed to investigate the differences in the mean values of continuous outcome measures, including the number of newly developed carious surfaces, dmfs scores, and non-vital/hypermobile teeth. Descriptive analyses will be used to report the proportions of adverse effects, as well as the levels of child and parental acceptance for each intervention. The McNemar test will be used to compare the changes in oral-health-related behaviours and children’s cooperation between different treatment groups.

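### Children's cooperation is tested only as a change between on-treatment scores, with a paired test, so a gel advantage that is constant from first use goes untested

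*Protocol article*

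**What the plan says.** Section 1.5 makes compliance a declared secondary outcome: "The secondary outcomes are parental satisfaction, children’s compliance, and adverse effects of the SDF therapy".

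Section 2.10 says when it is scored. A trained research assistant "will assess the children’s compliance during SDF therapy (solution or gel) using Venham’s behaviour-rating scale". Section 2.12 repeats this for the follow-up visits: "Children’s compliance with the SDF therapy will be assessed using Venham’s behaviour-rating scale". Neither section describes a score taken before, or apart from, an SDF application.

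Sections 2.7 and 2.9 fix the order of events. Envelopes are assigned once eligibility is confirmed, to give "effective allocation concealment prior to the administration of the assigned SDF intervention". After the blinded examination, "at baseline and follow-ups, another dentist will apply the assigned SDF formulation to all carious lesions". The first application is therefore made after randomisation and with the allocated product.

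Section 2.15 names one test for cooperation: McNemar is to "compare the changes in oral-health-related behaviours and children’s cooperation between different treatment groups". The same section plans a descriptive report, by arm, of child and parental acceptance, without a test.

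**The concern.** A change score is informative about treatment when its starting value precedes treatment. That holds for the oral-health behaviours named in the same sentence, because section 2.5 collects them by parental questionnaire at baseline and their starting value does not depend on the product. It does not hold for the Venham score, because the earliest score described already contains whatever the product does to the child's behaviour. Subtracting it removes any product effect present at first use.

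That is the kind of effect the protocol expects. The Discussion (section 3) attributes better acceptance to the gel's lack of odour and milder metallic taste, properties that would act at the first application. Section 1.2 lists children's compliance among the questions not yet investigated. The only inferential analysis named for that question could miss the expected effect.

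There is a second fault in the same sentence. McNemar compares paired binary observations on the same child. It can ask whether cooperation changed over time within one arm; it cannot compare two independent arms, and running it once per arm gives no estimate of the difference between them.

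**Working it through.** **The plan's own figures.** The article gives no figure for the cooperation analysis. Its sample size reproduces, which confirms the numbers of children used below:

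- Per arm: 2 × 0.765 × 0.235 × (1.960 + 1.282)² / 0.0765² ≈ 646 surfaces, so 1292 in total.
- Design effect: 1 + (4.75 − 1) × 0.227 = 1.851.
- Children: 1292 × 1.851 / 4.75 = 503.5; divided by (1 − 0.20), this gives 630, or 315 per arm.
- After 20% dropout: 315 × 0.80 = 252 per arm.

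**Why a constant effect cancels.** Let S₁ and S₂ be the expected cooperative shares on solution at an earlier and a later application, and let the gel add d at both. The between-arm difference in change is

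[(S₂ + d) − (S₁ + d)] − [S₂ − S₁] = 0,

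whatever d is and whichever two applications are chosen. If the gel adds d₁ at the earlier and d₂ at the later application, the difference is d₂ − d₁: only growth or decline of the advantage is tested.

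**Size under assumed rates.** The article gives no cooperation rates, so these are assumptions: binary cooperation, within-child correlation 0.5 on a latent scale, 252 per arm, two-sided 5% level, 4,000 simulated trials per row.

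| Cooperative share, solution | Cooperative share, gel | Test of change between arms | Test of levels, first visit | Test of levels, last visit |
|---|---|---|---|---|
| 60% → 60% | 75% → 75% | 5% | 95% | 95% |
| 60% → 70% | 75% → 85% | 5% | 95% | 99% |
| 60% → 75% | 75% → 86% | 14% | 95% | 88% |
| 60% → 60% | 65% → 75% | 54% | 22% | 96% |
| 60% → 60% | 60% → 75% | 86% | 5% | 95% |

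Hand check of the levels test in the first row:

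- Pooled share (0.60 + 0.75)/2 = 0.675.
- Null standard error √(2 × 0.675 × 0.325 / 252) = 0.0417.
- Alternative standard error √((0.24 + 0.1875)/252) = 0.0412.
- (0.15 − 1.96 × 0.0417)/0.0412 ≈ 1.66, which is a power of 0.95.

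In the first two rows the expected difference in change is exactly zero, so 5% is simply the false-positive rate. In the third row solution gains 15 points and gel 11, so the change favours solution by 4 points although gel is better at both visits.

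**McNemar run within each arm.** In the second row it rejects in 82% of trials on solution and 91% on gel. Both results reflect the shared improvement over time and say nothing about which product is better tolerated. In the first row, where the gel is 15 points better throughout, it rejects in 5% of trials in each arm.

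**The 0–5 scale.** The pattern is the same with an assumed ordinal distribution and a constant gel shift of 0.2 or 0.3 SD: comparing levels at the first application has 59% or 91% power, and comparing changes rejects in 5–6% of trials.

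**The case against.** A reader might infer that a real gel advantage could never show in this trial. The documents do not support that. Only the constant part cancels. If dislike of the solution builds up over repeated applications, which the Discussion's remarks on children's experience make plausible, the change test has 54% to 86% power in the last two rows of the table. A constant advantage would also be visible in the descriptive acceptance summaries, if these include the Venham scores, and describing a secondary outcome without testing it is a legitimate choice.

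A reader might also infer that the result would come out with the wrong sign. That needs an assumed habituation in which the solution arm has more room to improve. Even then rejection was only 14% in the third row, and 7–10% in the ordinal simulations with habituation of 0.3 SD, where mean changes differed by about 0.06 points (−0.32 on solution, −0.25 on gel). It is a possibility under assumptions and not a prediction.

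Section 2.15 does not say which visits define the change, and the schedule figure is not shown. Change from the first application is the natural reading but an inference. This matters less than it seems, because every Venham score described is on treatment and the cancellation applies to any pair of them.

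Finally, visit pairs and cut-points may be left to an analysis plan that is not shown. That would excuse missing detail. It does not excuse a stated comparison of changes, or a paired test assigned to a comparison between arms.

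**Conclusion.** The concern holds in a limited form. As written, section 2.15 gives no valid between-arm test of cooperation. If McNemar were replaced by a valid between-arm test of change, a gel advantage that is constant from first use would still go untested. Under the assumed 60% against 75% at every visit, that test has about 5% power, against about 95% for a comparison of levels. The figures rest on assumed cooperation rates and an assumed within-child correlation; the cancellation itself does not. The conclusion also takes the Venham score to be the cooperation measure meant in section 2.15 and assumes that no pre-treatment score exists outside the article. It concerns one secondary outcome.

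**What to change.** In section 2.15, replace the McNemar comparison of changes in cooperation with a between-arm comparison of Venham levels over all applications. An ordinal mixed model with arm, visit, arm-by-visit interaction and a random effect for child would do this. Report the arm difference overall and by visit, including the first application.

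The first application alone should not carry the comparison: in the last two rows of the table a test of levels there has only 22% and 5% power, so it would tend to miss an advantage that grows.

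Keep change from baseline for the questionnaire behaviours only, and name a valid between-arm test for them, since McNemar does not serve there either.

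The cost is a change of wording and slightly more analysis work. The scores are already planned at the applications, so no new data are needed.

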## 3. Discussion

This is a randomised, double-blind, active-controlled, parallel-group clinical trial that aims to investigate the comparative efficacy of semi-annual application of 38% SDF gel and 38% SDF solution for caries management in preschool children. Our objective is to compare the two SDF formulations in their caries-arresting effects over a 30-month period. Additionally, we will assess any adverse effects, parental satisfaction, and children’s compliance. The results of the trial will provide clinical evidence for clinicians to use 38% SDF gel to arrest ECC, especially for children who have difficulty in cooperation during the traditional dental treatment.

While SDF has been widely recognised as a cost-effective, simple, and non-invasive method in arresting carious lesions and a valuable tool in managing ECC, the traditional SDF aqueous solution has some limitations. The liquidity of solution may make the application on the carious lesions precisely challenging, increasing the risk of unintended soft tissue exposure and staining [28]. Additionally, the solution’s unpleasant metallic taste often stimulates salivary secretion, which may dilute or wash away the applied agent before it takes effect. This may diminish the overall caries prevention benefits and may negatively influence children’s experience and acceptance [29]. The 38% SDF gel formulation was therefore developed to address these drawbacks. The viscous, adhesive gel consistency is designed to better maintain the SDF at the carious lesions, reducing the risk of migration to adjacent areas and the potential for adverse effects. The gel formulation is also expected to be more resistant to rapid salivary dilution or mechanical expulsion, potentially improving overall caries arrest efficacy and children’s experience [30]. Notably, the SDF gel does not stain sound dentin or enamel, preserving the aesthetic appearance, though it can stain carious lesions, allowing for better monitoring of dental caries progression or regression [31]. Both the SDF gel and solution feature a blue tint, which enhances user-friendliness during the application process. Additionally, the SDF gel’s odourless nature and mitigation of the metallic taste make it more acceptable to preschool children, further enhancing its practicality in the clinical setting [32].

However, direct comparative evidence on the caries-arresting capacity and clinical efficacy of SDF gel versus the traditional SDF solution is limited. To address this evidence gap, this randomised controlled trial will employ a non-inferiority design to evaluate whether the SDF gel formulation is at least as effective as the standard SDF solution in arresting dental caries. We selected a 10% non-inferiority margin based on the existing literature and practical considerations in paediatric dentistry [33]. This margin allows us to assess clinical relevance while accommodating the challenges associated with sample size in the community. Given that this clinical trial requires the screening of approximately 3000 preschool children, the chosen margin strikes a balance between ensuring meaningful clinical outcomes and maintaining the feasibility of the trial. Furthermore, SDF gel may potentially offer additional benefits, such as improving application precision, reducing soft tissue staining, and enhancing patients’ acceptability. This study has large sample size which will provide adequate statistical power to detect any non-inferiority of the SDF gel compared to the SDF solution. Demonstrating the non-inferiority of SDF gel could support its clinical use, especially for paediatric patients among whom the precisely application of SDF therapies and extended contact time of the agents are prioritised. SDF gel also retains other advantages of SDF, such as affordability, accessibility, minimal invasiveness, and non-aerosol generation, making it an attractive option for public-health-oriented caries prevention and management strategies.

Overall, this study aims to provide robust clinical evidence on the effectiveness of 38% SDF gel in managing ECC. Confirming its non-inferiority to traditional SDF solution would promote its adoption, especially in public health contexts focused on paediatric oral care. The SDF gel’s affordability, ease of use, and minimal invasiveness offer a promising tool for advancing caries prevention strategies and improving children’s oral health worldwide.

## Figures and Tables

**Figure 1 dentistry-12-00419-f001:**
[figure not shown]
The schedule of enrolment, interventions, and assessments.

**Table 1 dentistry-12-00419-t001:** Venham’s behaviour-rating scale.

Score	Behaviour Rating
0	Total cooperation, best possible working conditions, no crying or physical protest.
1	Mild, soft verbal protest, or (quiet) crying as a signal of discomfort, but does not obstruct progress. Appropriate behaviour for procedure.
2	Protest more prominent. Both crying and hand signals. May move head around making it hard to administer treatment. Protest more distracting and troublesome. In contrast, child still complies with request to cooperate.
3	Protest presents real problem to dentist. Complies with demands reluctantly, requiring extra effort by dentist, body movement.
4	Protest disrupts procedure and requires that all of the dentist’s attention be directed toward the child’s behaviour. Compliance eventually achieved after considerable effort by dentist, but without much actual physical restraint.
5	Uncooperative. General protest, no compliance, or cooperation. Physical restraint is required.

## Data Availability

The results of the dental examination of each participating child will be shared with the parents or legal guardians via oral health reports. The team will share the results of the study with academia via publications and presentations. The datasets generated in this trial will be available from the primary investigator on a legitimate request.
